#### Acceptability

Consumer acceptability will be assessed in the postintervention survey using items from 8 of the UTAUT2 domains: performance expectancy, effort expectancy, social influence, facilitating conditions, hedonic motivation, trust, habit, and behavioral intention Multimedia Appendix 1 [66,68-91] [49,50,93,98]. The UTAUT2 has been widely applied to evaluate the adoption of consumer-facing technologies [50,93,99,100]. It has demonstrated strong internal consistency (Cronbach α range=0.637‐0.902 across domains) [93] and high reliability to evaluate acceptability (range ⍺=0.837‐0.899) [95]

Items are rated on a 7-point Likert scale, from 1 (“strongly disagree”) to 7 (“strongly agree”), with higher scores indicating greater acceptability. Six questions across 5 domains are shared between the 2 groups, with additional questions tailored to context-specific relevance depending on engagement levels. For example, in the performance expectancy domain, users respond to “I found the THRIVE program to be useful,” while nonusers respond to “I know what to do to stay healthy so I didn’t need this program.”

User participants will complete 18 items across the 8 UTAUT2 domains. Acceptability outcomes will be reported using the following 2 complementary metrics [51]: (1) the mean acceptability score across domains with scores of more than 4 considered indicative of acceptability (ie, responses in the “somewhat agree” to “strongly agree” range) and (2) the proportion of participants whose individual mean scores meet or exceed the threshold, with 70% or more representing a benchmark for acceptable uptake. Together, these metrics provide insights into both the overall perceived acceptability and the consistency of this perception across participants.

Nonuser participants will complete 12 items across 7 relevant domains (excluding “habit,” which is not applicable to those who did not engage with the intervention). The primary purpose of this analysis is to explore the domain-specific barriers to acceptability. First, item-level responses of more than 4 will be interpreted as indicating a potential concern within a specific domain. Second, we will report the proportion of nonusers whose mean domain scores are more than 4 to reflect broader patterns of perceived difficulty or lack of relevance.

These acceptability thresholds align with typical group-level acceptability criteria in other digital health evaluations [101,102] and were established a priori (Table 2).

**Table 2. T2:** Consumer extended unified theory of acceptance and use of technology 2 (UTAUT2) acceptability domains and threshold values.

Consumer participant acceptability measures		Users (number of items)^a^	Nonusers (number of items)^b^
UTAUT2 domains	Cronbach α		
Performance expectancy	0.833	3	1
Effort expectancy	0.902	2	4
Social influence	0.850	2	2
Facilitating conditions	0.773	3	1
Hedonic motivation	0.807	2	1
Habit	0.637	1	—^c^
Trust	0.830	4	2
Behavioral intention	0.901	1	1

a Acceptability threshold: mean score >4 and ≥70% participants meeting this threshold indicates acceptability.

b Barrier indicator: mean score >4 and ≥70% of participants meeting this threshold indicates a barrier to use.

c Not applicable.

Clinician acceptability will be assessed in the postintervention survey using 15 items drawn from 6 relevant UTAUT2 domains: performance and effort expectancy, social influence, facilitating conditions, trust, and behavioral intent Multimedia Appendix 1 [66,68-91]. These items reflect perceptions of program usefulness, its impact on care efficiency and/or remuneration, perceived barriers to consumer use, and the use of the clinician summary reports. Four survey items are negatively worded and will be reverse scored before analysis.

Acceptability outcomes will be reported using 2 complementary metrics, consistent with the approach for consumer participants. First, an overall mean acceptability score will be calculated across the 15 items. A mean score of more than 4 will be interpreted as indicating acceptability, representing a tendency toward “somewhat agree” or higher (Table 3). Second, we will report the proportion of clinicians whose individual mean score is more than 4, with 70% or more of participants meeting this threshold considered evidence of general acceptability [51]. These dual metrics allow both group-level and individual-level interpretation of findings. Additionally, domain-specific mean scores and proportions will also be calculated to explore patterns across the 6 UTAUT2 domains.

**Table 3. T3:** Clinician acceptability domains and cutoff scores.

UTAUT2^a^ domains	Number of items^b^
Performance expectancy	7
Effort expectancy	3
Social influence	1
Facilitating conditions	2
Trust	1
Behavioral intention	1

a UTAUT2: extended unified theory of acceptance and use of technology 2.

b Acceptability threshold: mean score>4 and ≥70% participants meeting this threshold indicates acceptability.

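### The six survey questions put to both users and nonusers are read in opposite directions in the two groups, and the article states no recoding for them

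*Protocol article*

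**What the plan says.** All references are to the protocol article, Outcomes, Acceptability, unless stated otherwise.

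- **Scale.** Consumer items run from 1 to 7, "with higher scores indicating greater acceptability". The sentence does not separate users from nonusers.
- **Shared items.** "Six questions across 5 domains are shared between the 2 groups, with additional questions tailored to context-specific relevance depending on engagement levels". The example that follows contrasts a user item with a nonuser item, so the two groups are users and nonusers.
- **Users.** "User participants will complete 18 items across the 8 UTAUT2 domains", and the first metric is "the mean acceptability score across domains with scores of more than 4 considered indicative of acceptability". Note a to Table 2 repeats this reading and adds the 70% benchmark.
- **Nonusers.** They answer 12 items in 7 domains, habit being left out. Here "item-level responses of more than 4 will be interpreted as indicating a potential concern within a specific domain". The share of nonusers with a domain mean above 4 is then reported as a sign of difficulty or lack of relevance. Note b to Table 2 says: "Barrier indicator: mean score >4 and ≥70% of participants meeting this threshold indicates a barrier to use".
- **Recoding.** The only statement on reverse scoring concerns the clinician survey: "Four survey items are negatively worded and will be reverse scored before analysis".

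**The concern.** Reading agreement as a barrier suits the tailored nonuser items. The one the article quotes has the respondent say that the program was not needed, so agreement is indeed unfavourable. It does not suit a question that users also answer in the same words. A single question cannot show acceptability above 4 in one group and a barrier above 4 in the other unless it is recoded in one of them. The nonuser rule also conflicts with the general direction given for the consumer scale.

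Acceptability is a component of the primary feasibility outcome (Table 1), and the stated main purpose of the nonuser analysis is to explore barriers domain by domain. If the rules are followed as written and the shared items are favourably worded, approving answers from nonusers are listed as concerns and disapproving answers to the same questions are not. If any shared item is unfavourably worded, the error falls instead in the user acceptability score.

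**Working it through.** **1. Item counts (Table 2).**
Users: 3 + 2 + 2 + 3 + 2 + 1 + 4 + 1 = 18 items in 8 domains.
Nonusers: 1 + 4 + 2 + 1 + 1 + 2 + 1 = 12 items in 7 domains.
Both totals agree with the text. The six shared questions are 6/12 = 50% of the nonuser items and 6/18 = 33% of the user items.

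**2. One answer under both rules.** Take a response of 6 to a shared question, with no recoding.

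| Wording of the item | In a user, 6 counts toward | In a nonuser, 6 counts as | Group scored backwards |
|---|---|---|---|
| Favourable | acceptability (right) | potential concern (wrong) | nonusers |
| Unfavourable | acceptability (wrong) | potential concern (right) | users |

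Exactly one group is wrong in each row, so the conflict does not depend on the wording. Only the identity of the group does.

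**3. Nonuser domains made up only of shared questions.** Assume that the single nonuser performance-expectancy item is the tailored one quoted in the article. The five shared domains then come from six: effort expectancy, social influence, facilitating conditions, hedonic motivation, trust and behavioral intention. Choosing five of six leaves out one. Three of the six (facilitating conditions, hedonic motivation, behavioral intention) have a single nonuser item, so at least 3 − 1 = 2 single-item domains rest wholly on a shared question.

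Listing every allocation of six questions to five of these domains that fits the item counts gives 15 allocations. In each, between 2 and 4 nonuser domains consist only of shared questions. Without the performance-expectancy assumption there are 45 allocations and the range is 2 to 5, so the minimum of 2 does not change.

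**4. Mixed domains.** As an illustration, suppose that two of the four nonuser effort items are shared and favourably worded, and that the other two are tailored barrier items. Answers are listed with the shared items first, and reversal means 8 minus the score.

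| Nonuser | Answers | Domain mean as written | Shared items reversed | Domain mean after reversal |
|---|---|---|---|---|
| Finds it hard | 2, 2, 6, 6 | 16/4 = 4.0 | 6, 6, 6, 6 | 24/4 = 6.0 |
| Finds it easy | 6, 6, 2, 2 | 16/4 = 4.0 | 2, 2, 2, 2 | 8/4 = 2.0 |

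As written, the domain mean does not separate the two respondents, and neither mean exceeds 4. The item-level rule does flag both. It flags the first on the two tailored items, which is right, and the second on the two shared items, which is wrong. The first respondent's unfavourable answers to the shared items are not flagged.

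**The case against.** The strongest reply is that a scoring key belongs in the survey appendix or the SAP. The SAP is to be independently reviewed and preregistered before data extraction (Quantitative Data), and the clinician sentence shows that the authors know about reverse scoring. This stands in part: the shared items may yet be recoded, so it cannot be said that the data will be mis-scored. But the article does more than leave a detail out. It states the scale direction and both thresholds, calls the thresholds a priori, and applies the barrier reading to the nonuser items without exception. Those statements conflict as they stand.

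Four stronger readings are tempting and are not supported.

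- *Nonusers are the group scored backwards.* No shared question is quoted, and the wording is in Multimedia Appendix 1, which was not available for this review.
- *Real barriers would go unseen.* The tailored items remain visible under the item-level rule, and nonusers are also sampled for interview (Engagement). What is lost is the meaning of the shared items and of the domain means that contain them.
- *A planned comparison of users with nonusers is invalid.* The Primary Outcome Analyses section plans comparison between user subgroups, which need not include nonusers. Raw answers to identical questions also stay comparable, whatever label is put on scores above 4.
- *The progression decision would be misdirected.* Progression Criteria does not name the nonuser barrier indicator, uses no binary rule, and weighs engagement and acceptability together with qualitative findings.

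**Conclusion.** The point holds on the article's own text. For the six shared questions, the same answer is read as acceptability in users and as a concern or barrier in nonusers. Whatever the wording, one group is scored backwards unless a recoding is applied that the article does not state.

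Half of the nonuser items (6 of 12) are affected, and at least two single-item nonuser domains rest entirely on a shared question. The cancellation in mixed domains is an illustration that assumes two shared, favourably worded effort items. The tailored nonuser items are handled correctly.

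This should be fixed, but it is not critical. The nonuser analysis is exploratory, and progression also relies on qualitative data.

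**What to change.** Before data extraction, put a direction key for every consumer item in the SAP, set from the item wording in Multimedia Appendix 1. Then:

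1. For each favourably worded shared item, either reverse it (8 minus score) before the nonuser barrier rule is applied, or leave it out of the nonuser barrier means and report it in the acceptability direction.
2. For any negatively worded shared item, reverse it in the user acceptability score instead.
3. Limit note b of Table 2, and the item-level rule in the text, to items scored in the barrier direction.
4. If users and nonusers are compared, use only the six shared items, scored the same way in both groups.

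The cost is a scoring key in the SAP and a sentence in Table 2 and in the text. The survey does not change, and no further data are needed. Setting the key before extraction also keeps the claim that the thresholds were fixed a priori.

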#### Clinician Sampling and Recruitment

All general practitioners and general practice nurses from participating practices will be invited to take part in the preintervention and postintervention interviews and the postintervention survey. Clinician participation will be entirely voluntary. Study information, including a QR code link to the survey or consent form, will be emailed to potential participants by the practice. Additionally, a QR code linking to the survey or consent form will be displayed in the practice staff areas.

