#### Clinician Participants

All clinicians from all participating practices will be invited to participate. The clinician sample size will be pragmatic and guided by the study objectives, given the outcomes being measured.

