#### Clinician Data Collection

Preintervention and postintervention clinicians will be invited to participate in semistructured interviews. These interviews will explore key feasibility domains such as acceptability, sustainability, perceived impact, and optimization strategies. Approximately 8 to 10 clinicians (2 per practice) will be interviewed via videoconference, with sampling guided by saturation. Interviews will be guided by qualitative descriptive methodology. Interview guides are included in Multimedia Appendix 1 [66,68-91]. The time commitment for clinicians will range from 10 to 40 minutes, depending on their level of participation across survey and interview components.

Clinicians will also complete a postintervention survey. The survey includes 15 items rated on a 7-point Likert scale and captures data on intervention acceptability, perceived usefulness, and ease of implementation, impact on workflow, barriers, and summary of use.

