### Outcomes

#### Overview of Outcome Measures

The primary focus of this study is feasibility, which will be assessed through consumer and clinician engagement, acceptability, and perceived sustainability (Table 1). A secondary outcome is preliminary effectiveness, evaluated through changes in consumer activation, self-rated health, and disease risk scores.

**Table 1. T1:** Overview of outcome measures.

Outcome and components	Data collection tool	Participants	Collection timeframe
Primary outcome (feasibility)			
Engagement	Usage logs from THRIVE platform	Consumers	Observation period
Acceptability	UTAUT2^a^ survey questions [93-95]	Consumers and clinicians	Postintervention
Sustainability	Semistructured interviews	Consumers and clinicians	Postintervention
Secondary outcomes (effectiveness)			
Consumer activation	CHAI^b^ survey questions [96]	Consumers	Preintervention and postintervention
Self-rated health	Single-item Likert Scale survey question	Consumers	Preintervention and postintervention
Calculated disease risk scores	AUSDRISK^c^ [70] and AusCVDRisk^d^ [71] scores calculated from THRIVE data	Consumers	Observation period

a UTAUT2: extended unified theory of acceptance and use of technology 2.

b CHAI: Consumer Health Activation Index.

c AUSDRISK: The Australian Diabetes Risk Score.

d AusCVDRisk: The Australian Cardiovascular Disease Risk Score.

The consumer baseline survey will also capture factors that may influence engagement with the intervention, including sociodemographic characteristics, perceived disease threat, and trust in the therapeutic relationship. Perceived disease threat will be measured using 4 validated items from the UTAUT2 framework [93], rated on a 7-point Likert scale ranging from “strongly disagree” to “strongly agree” (⍺=0.817). Trust in the therapeutic relationship will be assessed using the Trust in Physician Short-Form Scale [97]. These baseline variables will form the a priori covariate set for exploratory quantitative analyses examining predictors of engagement with the THRIVE intervention and potential signals of change in secondary outcomes. They will also be used to inform question refinement for the postintervention interviews, ensuring representation of diverse experiences and perspectives across engagement levels.

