### Data Management

The THRIVE dashboard and clinician summary report are visible only to the consumer participant through their secure, personalized link. No identifiable or dashboard data are shared with clinicians or transferred to general practice systems. Only the consumer participant can choose to share their outputs or the clinician report.

Identifiable consumer participant information (first name and email address) will be collected solely to link preintervention and postintervention data. These identifiers will be collected within the secure University of Wollongong Qualtrics survey platform and stored separately from other study data. An independent research officer will assign each participant a unique study code to enable matching of deidentified data across time points. The linkage file containing names, emails, and study codes will be stored separately from all study datasets and will be accessible only to the independent research officer. Once the linkage process is complete, only deidentified datasets will be stored in the University of Wollongong Microsoft Teams environment, consistent with institutional data governance policies. For the interviews, the interviewer will have access to participants’ names and email addresses for scheduling and conducting interviews. Audio recordings and transcripts will be stored securely in the Microsoft Teams environment, consistent with institutional data governance policies. The research officer will deidentify transcripts and assign interview codes. These codes will be independent of those used for the quantitative data. Only deidentified data will be used for analysis.

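### The clinician acceptability benchmark pools clinicians who encountered THRIVE with those who did not, and clinician engagement is named as primary but defined only for consumers

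*Protocol article*

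**What the plan says.** **Who is surveyed.** Under Clinician Sampling and Recruitment, "All general practitioners and general practice nurses from participating practices will be invited to take part" in the interviews and the postintervention survey. Participation is voluntary. On numbers, the Clinician Participants section says: "The clinician sample size will be pragmatic and guided by the study objectives".

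**How a report reaches a clinician.** Data Management states: "No identifiable or dashboard data are shared with clinicians or transferred to general practice systems", and then: "Only the consumer participant can choose to share their outputs or the clinician report". The Intervention sections agree that sharing the clinician report is the consumer's option.

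**How clinicians are scored.** In the Acceptability section: "First, an overall mean acceptability score will be calculated across the 15 items", with a mean above 4 read as acceptable. The second metric is: "we will report the proportion of clinicians whose individual mean score is more than 4, with 70% or more of participants meeting this threshold" taken as general acceptability. Table 3 repeats both thresholds. The section describes this as consistent with the consumer approach.

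**How consumers are scored.** Users answer 18 items and nonusers 12. In Table 2 a high score means acceptability for users and a barrier for nonusers. The habit domain is dropped for nonusers because it does not apply to people who did not engage.

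**Engagement.** The Overview of Outcome Measures describes the primary focus as "feasibility, which will be assessed through consumer and clinician engagement, acceptability, and perceived sustainability". In Table 1 the Engagement row has one tool, platform usage logs, and one group, consumers. The Engagement section builds its levels from those logs alone.

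**What is collected on clinician use.** Among other content, the clinician survey captures "impact on workflow, barriers, and summary of use".

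**The concern.** Several clinician items concern usefulness, effect on care efficiency and use of the summary report. A clinician who has met neither a report nor a patient using THRIVE can answer these only by expectation. The benchmark puts such answers in the same numerator and denominator as opinions formed in use. The plan recognises this distinction for consumers, so leaving it out for clinicians departs from its own logic.

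Two things are at stake. A clinician pass could reflect general goodwill toward a prevention tool, and a clinician fail could reflect indifference among people the tool never reached. These call for different responses: one concerns the product, the other its delivery. Separately, the text lists clinician engagement within the primary outcome but attaches no measure to it, so the proportion of clinicians reached has no assigned place in the results, although the survey asks about use.

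**Working it through.** **1. No plan figure to reproduce.** The cut-offs of 4 and 70% are chosen benchmarks, and no clinician sample size or precision is stated. The check is therefore a comparison of passages followed by illustrations on stated assumptions.

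**2. Passages side by side.**

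| | Consumers | Clinicians |
|---|---|---|
| Route to exposure | Own use of the platform | A patient's choice to share, or discussion and referral |
| Split by use | Yes, separate items and readings | None stated |
| Denominator for 70% | Users and nonusers separately (Table 2) | All responders (Table 3) |
| Engagement measure (Table 1) | Usage logs | None assigned |

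**3. A neutral responder.** On a 7-point scale an answer of 4 stays 4 after reverse scoring (8 − 4 = 4). A clinician who answers 4 throughout therefore has a mean of exactly 4.0. The rule requires more than 4, so this clinician counts against the 70%.

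**4. Pooled proportion.** Let e be the share of responders exposed, p1 the proportion above 4 among the exposed and p0 among the unexposed. Then pooled = e × p1 + (1 − e) × p0. All values below are assumptions.

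| Case | e = 75% | e = 50% | e = 25% |
|---|---|---|---|
| A: p1 = 50%, p0 = 85% | 58.8% | 67.5% | 76.2% (pass) |
| B: p1 = 85%, p0 = 50% | 76.2% (pass) | 67.5% | 58.8% |
| C: p1 = 80%, p0 = 0% (all neutral) | 60% | 40% | 20% |

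For example, case A at e = 25% is 0.25 × 0.50 + 0.75 × 0.85 = 0.7625. In A the benchmark is passed although only half of exposed clinicians approve. In B it fails at e = 50% although 85% of them do. Case C is the extreme: a pass needs e of at least 0.70/0.80 = 87.5%.

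The group mean behaves differently. If the unexposed average 4.0 and the exposed average m above 4, the pooled mean is 4 + e(m − 4), which exceeds 4 for any e above zero. The two metrics can then disagree purely because of exposure.

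**5. How many might see no report.** From the plan: 215 consumers and 50% completing the assessment, so 215 × 0.5 = 107.5 possible reports. Assumptions: a fraction s of completers share, each with one clinician, spread evenly at random over C clinicians. C = 25 corresponds to five practices with the five GPs that are prioritised as a minimum; C = 50 allows for larger practices and nurses. Expected share seeing at least one report = 1 − (1 − 1/C)^(107.5 × s).

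| s | Reports shared | C = 25 | C = 50 |
|---|---|---|---|
| 10% | 10.75 | 36% | 20% |
| 20% | 21.5 | 58% | 35% |
| 50% | 53.75 | 89% | 66% |

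A sizeable unexposed fraction is plausible unless sharing is common. The table counts reports only, so exposure through discussion would raise these figures.

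**6. Precision of an exposed subgroup.** At s = 10% and C = 25, about 25 × 0.355 = 9 clinicians would have seen a report. For 7 of 10, the Wilson 95% interval has centre (0.70 + 3.84/20)/(1 + 3.84/10) = 0.645 and half-width 1.96 × √(0.70 × 0.30/10 + 3.84/400)/1.384 = 0.248, or about 40% to 89%.

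**The case against.** The strongest reply is that clinician use is measured. The survey records it, the acceptability items touch on use of the summary reports, and clinicians are interviewed before and after. This stands. A reader might infer that nothing captures clinician engagement, and the documents do not support that. What remains is narrower: the information is neither assigned to the engagement outcome nor used to separate responders. Items on report use also appear to sit inside the acceptability score, which mixes exposure with opinion. The stated objective on engagement, to examine what influences it, can be served by interviews and does not by itself promise an endpoint; the mismatch is between the Overview of Outcome Measures and Table 1.

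A reader might also infer that a shared report is a clinician's only contact with THRIVE. That goes too far. Clinicians may encourage or refer patients, each practice has an informed champion, and patients can talk about THRIVE without handing over a report. Some items, such as remuneration and barriers to consumer use, can be answered without having seen one. Responders to a voluntary survey may also be more exposed than nonresponders.

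Nor does the clinician benchmark decide progression. The framework has three levels, reads indicators alongside qualitative findings, expects modification as the usual path, and requires several shortfalls plus fundamental concerns before redesign.

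Finally, item wording and any skip logic are in an appendix that is not shown, and so is the SAP. Either may handle unexposed clinicians. The analysis section compares acceptability between user subgroups but names none for clinicians. This limits certainty, but it does not alter the unqualified denominator in the Acceptability section and Table 3, or the consumers-only Engagement row.

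**Conclusion.** The point holds in a limited form. As written, the clinician mean and 70% benchmark pool all responders regardless of exposure, exposure to reports depends on consumer choice, and the plan makes the corresponding split for consumers only. A pooled pass or fail can therefore be driven by clinicians who never encountered THRIVE. The direction is unknown: in the illustrations, a true 50% among exposed clinicians appears as 76%, and a true 85% as 67.5% or 59%. These sizes rest on assumed sharing rates, clinician numbers and scores by exposure; only the 215 consumers, the 50% completion, the five practices and the minimum of five GPs come from the plan.

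The engagement mismatch is a matter of text and needs no assumption: clinician engagement is within the primary feasibility outcome, but no clinician measure is attached to it. Neither issue invalidates the study. Both weaken the reading of a primary feasibility result and can be corrected cheaply.

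**What to change.** 1. Classify each clinician responder as exposed (saw at least one THRIVE report or discussed THRIVE with a patient) or unexposed. Use the survey's existing content on use or, if that does not allow it, add one yes/no item.
2. Report the mean and the 70% benchmark for exposed and unexposed clinicians separately, with denominators, alongside the pooled figure. Read acceptability in use from the exposed group. Keeping the pooled figure matters, because an exposed-only headline would drop the clinicians THRIVE failed to reach and would depend on which patients chose to share.
3. Add a clinician line to the Engagement row of Table 1: the proportion of responding clinicians exposed, by practice.

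The cost is at most one survey item and a few lines of text, settled before the postintervention survey opens. The statistical price is small subgroup denominators with wide intervals, such as 40% to 89% for 7 of 10, so subgroup results should carry intervals and be read descriptively.
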